## MATERIAL AND METHOD

### Study Design

This is a clinical trial protocol, controlled, randomized, single-blind with two groups, an allocation ratio of 1:1, and a hypothesis of superiority that will be carried out with patients admitted to the adult Intensive Care Unit (ICU) of the University Hospital Onofre Lopes (HUOL) with the clinical diagnosis of acute myocardial infarction. Figure 1 represents the follow-up flowchart of the study according to CONSORT (Consolidated Standards of Reporting Trials) (49). Figure 2 presents the flowchart with the main stages of the study.

[figure not shown]

**Fig. 1** – Study flowchart according to the Consolidated Standards of Reporting Trials (CONSORT).

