## **Randomization and blinding**

The randomization sequence will be generated by software available online at [www.randomizer.org](http://www.randomizer.org) by a study collaborator not involved in the processes of collecting or evaluating the results. The software will generate a sequence of uniformly random numbers for 2 groups. The sequence generated by the program will be placed in opaque envelopes and numbered sequentially. The opaque and sealed envelopes will only be under the domain of the researcher responsible for the randomization. Only the collaborators in charge of administering the intervention protocol will be aware of each participant's allocation group. Furthermore, all

outcome assessors will remain blinded during the study to participant allocation.

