In step 2, patients will follow early exercise-based cardiac rehabilitation performed following all prescription parameters (FITT-VP) and safety criteria recommended by ACSM, 2018 (33). The institutional protocol (**Appendix B**) will be performed with a **frequency** of 2 sessions per day, during the entire hospitalization, with an average of 8 to 10 total sessions; Low **intensity** for aerobic training with METs estimated by the subjective perception of effort of BORG between 9 to 12 reaching between 2 to 3 METs and for resistance training with 2 to 3 series of 60% of the maximum repetitions reached in the 30s sit-to-stand test; **Type** of exercises involved will be aerobic training using the cycle ergometer associated with resistance training using the body's own weight with functional sit-to-stand training; Aerobic training **time** ranging from 3 to 20 minutes. The **Volume or Dose** of aerobic training will be measured by calculating the training dose per session and the total dose applied during hospitalization, providing a value in time x intensity (METs) x frequency of accumulated sessions and total number of sessions x time. The structured **progression** in the protocol focuses on the time of aerobic exercise and the number of series of resistance training. The exercise sessions will follow the protocol presented, however, present individualized prescriptions based on tolerance time during aerobic training with a cycle ergometer and resistance training from the maximum number of repetitions reached in the 30s TSL evaluated

individually before randomization.

Before hospital discharge, patients in the intervention group will receive an exercise guidance booklet (Appendix C) to perform step 3 of semi-supervised and continued cardiac rehabilitation with the exercise time reached at the end of in-hospital rehabilitation, frequency of 5 x per week and progression of 5 minutes each week within the first month after hospital discharge, according to tolerance and self-monitoring of intensity through perceived exertion using the Borg scale, maintained between 9 to 12, to ensure light exercise to moderate intensity. In this phase, patients in the intervention group will be monitored weekly by telephone and will receive a diary (Appendix C) to record the time of daily and weekly activity that they must deliver when investigating when they return for reassessment 30 days after hospital discharge.

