### Cardiohemodinamic safety of early cardiac rehabilitation

The safety of the institutional protocol tested in this trial will occur through notifications

of adverse events during and after the CR sessions provided to patients in the intervention group. We will report adverse events session by session, listing the main ones: arrhythmias, chest pain, borg>13, drop in systolic blood pressure (SBP) above 10 mmHg, and cardiorespiratory arrest. Other events not previously listed will also be recorded in the patient follow-up and evaluation form as per Appendix A.

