## BUDGET ESTIMATED (formulary according to the local ethical committee)

| Permanent Material                        |            |          |                 |
|--------------------------------------------------|------------|----------|-----------------|
| Item                                             | Unit price | Quantity | Total (R\$)     |
| Treadmil (Centurion 300)                         | 995,00     | 1        | 995,00          |
| Stethoscopy (Littmam)                            | 500,00     | 1        | 500,00          |
| Pulse Oxymeter (Nonin Onyx- 9500)                | 300,00     | 1        | 300,00          |
| Chest strap heart frequency meter (H10 – POLAR)  | 500,00     | 2        | 1.000,00        |
| Notebo"r 14" DELL inspiron 14-2630 preto core i3 | 2.400,00   | 1        | 2.400,00        |
| Subtotal                                  |            |          | 5.195,00 |

| Material de consumo
No-permanent |            |          |               |
|---------------------------------------------|------------|----------|---------------|
| Item                                        | Unit price | Quantity | Total (R\$)   |
| Toner Printer                               | 45,00      | 1        | 90,00         |
| paper A4                                    | 15,00      | 3        | 45,00         |
| Pencil (box)                                | 10,00 1cx  | 1cx      | 10,00         |
| Plastic folder                              | 5,00       | 3        | 15,00         |
| Eletcrodes for ECG (Meditrace)              | 40,00 cx   | 10       | 400,00        |
| Paper envelopes                             | 73,00 cx   | 1        | 73,00         |
| Subtotal                             |            |          | 633,00 |

Resources spent on consumables and permanent materials amount to R\$ 5,828.00. Part of these expenses, referring to permanent materials, are institutional assets and are available for research. The rest of the amount will be entirely the responsibility of the researcher. In addition to permanent and consumable materials, the study will require the use of the sector's telephone (CORE-HUOL) to make calls to patients in the semi-supervised rehabilitation phase and call for reassessment.

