**PHYSICAL EXAMINATION PER SESSION**

**Session 1:** Session start: HR:\_\_\_\_\_bpm RF:\_\_\_\_\_bpm SpO2:\_\_\_\_\_ % BP:\_\_\_\_\_mmHg  
End of session: HR:\_\_\_\_\_bpm RF:\_\_\_\_\_bpm SpO2:\_\_\_\_\_ % BP:\_\_\_\_\_mmHg  
Security: ☐ Angina ☐ Arrhythmia \_\_\_\_\_ ☐ Borg>=13 ☐ Fall of SBP>=10mmHg  
☐ CPA ☐ Others:\_\_\_\_\_ Vasoactive drug (Dose) ☐ \_\_\_\_\_ Devices:\_\_\_\_\_  
\_\_CR summary:\_\_\_\_\_

**Session 2:** Session start: HR:\_\_\_\_\_bpm RF:\_\_\_\_\_bpm SpO2:\_\_\_\_\_ % BP:\_\_\_\_\_mmHg  
End of session: HR:\_\_\_\_\_bpm RF:\_\_\_\_\_bpm SpO2:\_\_\_\_\_ % BP:\_\_\_\_\_mmHg  
Security: ☐ Angina ☐ Arrhythmia \_\_\_\_\_ ☐ Borg>=13 ☐ Fall of SBP >=10mmHg  
☐ CPA ☐ Others:\_\_\_\_\_ Vasoactive drug (Dose) ☐ \_\_\_\_\_ Devices:\_\_\_\_\_  
\_\_CR summary:\_\_\_\_\_

**Session 3:** Session start: HR:\_\_\_\_\_bpm RF:\_\_\_\_\_bpm SpO2:\_\_\_\_\_ % BP:\_\_\_\_\_mmHg  
End of session: HR:\_\_\_\_\_bpm RF:\_\_\_\_\_bpm SpO2:\_\_\_\_\_ % BP:\_\_\_\_\_mmHg  
Security: ☐ Angina ☐ Arrhythmia \_\_\_\_\_ ☐ Borg>=13 ☐ Fall of SBP >=10mmHg  
☐ CPA ☐ Others:\_\_\_\_\_ Vasoactive drug (Dose) ☐ \_\_\_\_\_ Devices:\_\_\_\_\_  
\_\_CR summary:\_\_\_\_\_

**Session 4:** Session start: HR:\_\_\_\_\_bpm RF:\_\_\_\_\_bpm SpO2:\_\_\_\_\_ % BP:\_\_\_\_\_mmHg  
End of session: HR:\_\_\_\_\_bpm RF:\_\_\_\_\_bpm SpO2:\_\_\_\_\_ % BP:\_\_\_\_\_mmHg  
Security: ☐ Angina ☐ Arrhythmia \_\_\_\_\_ ☐ Borg>=13 ☐ Fall of SBP >=10mmHg  
☐ CPA ☐ Others:\_\_\_\_\_ Vasoactive drug (Dose) ☐ \_\_\_\_\_ Devices:\_\_\_\_\_  
\_\_CR summary:\_\_\_\_\_

**Session 5:** Session start: HR:\_\_\_\_\_bpm RF:\_\_\_\_\_bpm SpO2:\_\_\_\_\_ % BP:\_\_\_\_\_mmHg  
End of session: HR:\_\_\_\_\_bpm RF:\_\_\_\_\_bpm SpO2:\_\_\_\_\_ % BP:\_\_\_\_\_mmHg  
Security: ☐ Angina ☐ Arrhythmia \_\_\_\_\_ ☐ Borg>=13 ☐ Fall of SBP >=10mmHg  
☐ CPA ☐ Others:\_\_\_\_\_ Vasoactive drug (Dose) ☐ \_\_\_\_\_ Devices:\_\_\_\_\_  
\_\_CR summary:\_\_\_\_\_

**Session 6:** Session start: HR:\_\_\_\_\_bpm RF:\_\_\_\_\_bpm SpO2:\_\_\_\_\_ % BP:\_\_\_\_\_mmHg  
End of session: HR:\_\_\_\_\_bpm RF:\_\_\_\_\_bpm SpO2:\_\_\_\_\_ % BP:\_\_\_\_\_mmHg  
Security: ☐ Angina ☐ Arrhythmia \_\_\_\_\_ ☐ Borg>=13 ☐ Fall of SBP >=10mmHg  
☐ CPA ☐ Others:\_\_\_\_\_ Vasoactive drug (Dose) ☐ \_\_\_\_\_ Devices:\_\_\_\_\_  
\_\_CR summary:\_\_\_\_\_

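### The stated assessor blinding is not protected, and is likely to be broken, at the 30-day visit, where only intervention patients hand in a diary and one form carries both the session log and the test results

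*Protocol*

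**What the plan says.** The Study Design section describes the trial as "controlled, randomized, single-blind with two groups, an allocation ratio of 1:1". Randomization and blinding then divides the roles: "Only the collaborators in charge of administering the intervention protocol will be aware of each participant's allocation group", and all "outcome assessors will remain blinded during the study to participant allocation". The section on the 30-second chair sit-to-stand test (30CST) repeats the promise for the principal investigator, who administers that test.

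Two other parts of the protocol bear on whether this can be kept.

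- **Diary.** Early cardiac rehabilitation program says that "patients in the intervention group will be monitored weekly by telephone and will receive a diary (Appendix C"), and that the diary serves to "record the time of daily and weekly activity that they must deliver when investigating when they return for reassessment 30 days after hospital discharge". Controls have no diary.
- **Form.** Appendix A has a part titled "PHYSICAL EXAMINATION PER SESSION", with eight session blocks. Each holds vital signs, safety boxes and a line summarising the rehabilitation given. The same form goes on to the result fields for MRI, heart rate variability (HRV), 30CST and CPET. The safety section adds that events not on its list "will also be recorded in the patient follow-up and evaluation form as per Appendix A".

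**The concern.** Patients can hardly be unaware of a supervised exercise programme followed by a home programme with weekly calls. Blinding of the person who runs the test is therefore the main guard against expectation affecting the measurement.

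Two outcomes at the 30-day visit depend on effort. The CPET runs until the participant judges that they cannot go on. The 30CST is done at full speed and counted by the evaluator on the spot. A tester who knows the arm could, without intending it, encourage harder, accept a later or earlier stop, or count a doubtful repetition. In a superiority trial that expects benefit, the likely direction favours the intervention, and an effort test affected in this way cannot be repaired in the analysis.

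**Working it through.** The protocol gives no figure on this point to reproduce, so the check compares its parts.

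**1. Which visit receives the diary.** Data collection procedures places the second assessment from day 30 after discharge, at the outpatient return. The 30CST and HRV sections put their repeat measurements there. The CPET is described as a test after rehabilitation, and Appendix A has a CPET field numbered 2 and none numbered 1. This places the CPET at the same visit; the assessment timeline figure is not available to confirm it.

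**2. What comes to that visit, by arm.** The sample size section plans 12 per group.

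| | Intervention | Control |
|---|---|---|
| Diaries, everyone attending | up to 12 of 12 | 0 of 12 |
| Diaries, after the 30% losses allowed for (12 × 0.70 = 8.4) | about 8 | 0 |

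These rows count diaries, not unblinded assessors. They show only that the object separates the arms completely if the procedure is followed.

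**3. What the form shows.** The Appendix A header has a date for the evaluation and one for the re-evaluation, so the form is meant to be reopened at follow-up. Both groups do STEPS 1 to 3 of the inpatient protocol, and only the intervention group goes on to STEP 4 and beyond. Early session entries alone therefore need not reveal the arm. An entry or summary describing STEP 4 or later would, and so could events noted for sessions that only the intervention group receives.

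**4. What safeguard is written.** The protocol does not name the person who takes the diary, say that the session pages are withheld from whoever enters the 30-day results, or tell patients to keep their group to themselves. Filmed scoring by ten trained raters covers only the 30CST at ICU discharge, so it does not protect the 30-day count.

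**5. Where an influence would enter the analysis.** Statistic Strategy compares the groups directly for the CPET only. For 30CST, MRI and HRV it describes paired tests within each group. The sample size also rests on oxygen consumption. With no baseline CPET field, an influence at this single visit passes straight into the between-group difference.

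**6. What a bias would do, if there were one.** The documents give no bias size and no SD, so this is conditional arithmetic and not an estimate. Suppose there is no true effect and the test conditions favour the intervention by b standard deviations. A two-sided 5% independent t-test with n per group then has 2n − 2 degrees of freedom and noncentrality b × √(n/2). For n = 12, √6 = 2.449; for n = 8, √4 = 2.

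| Assumed b | Noncentrality, n = 12 | Rejection rate, n = 12 | Noncentrality, n = 8 | Rejection rate, n = 8 |
|---|---|---|---|---|
| 0 | 0 | 5.0% | 0 | 5.0% |
| 0.2 | 0.49 | 7.6% | 0.40 | 6.6% |
| 0.3 | 0.73 | 10.8% | 0.60 | 8.7% |
| 0.5 | 1.22 | 21.6% | 1.00 | 15.4% |

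**The case against.** The strongest reply is that every instruction can be followed as written without any assessor learning the arm. The protocol already separates those who deliver the intervention from those who measure outcomes. It says when the diary is returned but not to whom, so an unblinded collaborator could take it. One form is likewise not one reader: the session log and the test results are separate sections, and nothing says that the tester holds the completed session pages. This stands, and it rules out saying that blinding fails.

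It also stands against two inferences that a reader might draw.

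- *Sessions 4 to 8 are filled in for one arm only.* The form numbers sessions and Appendix B numbers STEPS. No text equates the two or says that a STEP is never repeated, and both groups exercise until they leave the ICU. Control entries need not end at the third session.
- *The rehabilitation unit's telephone unblinds the CPET.* The budget section says that "the study will require the use of the sector's telephone (CORE-HUOL) to make calls to patients in the semi-supervised rehabilitation phase and call for reassessment", and CPETs are done in the same unit. A shared telephone does not show shared staff, and the note also covers recalling patients for reassessment. It is no evidence of unblinding.

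For the CPET, peak oxygen consumption comes from a gas analyser, the ramp protocol is the same for all, and stopping follows published criteria. This narrows the room for influence but does not close it, because the end point of the test remains the participant's effort.

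The last reply, that diary collection and form layout are operational details outside a protocol, does not stand here. This protocol fixes both the timing of the hand-in and the layout of the form, and in a way that works against its own blinding statement.

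**Conclusion.** The concern holds in a limited form. Assessor blinding is stated but not protected, and the procedures as written make it likely to be broken at the 30-day visit. They bring arm-revealing material, the diary and possibly the later session entries, to the point where effort-dependent outcomes are recorded.

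The 30-day 30CST is exposed because it is counted live. The CPET is exposed because it is limited by effort, has no baseline field and carries the only specified comparison between groups.

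This rests on three assumptions: that patients know their arm, that the CPET belongs to the 30-day visit, and that no unwritten arrangement already keeps the diary and session pages from the testers. If such an arrangement exists, it only needs to be written down. The size of any bias cannot be derived from the documents, and the conditional rates above should not be read as a forecast.

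**What to change.** Four changes, best made before the first patient reaches the 30-day visit:

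1. Split Appendix A. Sessions, doses and session events go into a treatment record kept by the unblinded intervention collaborators. The 30CST, HRV, MRI and CPET results go on a separate outcome form with no session data.
2. Amend the step 3 text so that the diary is given to an unblinded intervention collaborator, away from the assessor, after all 30-day tests are finished.
3. Instruct patients not to tell the tester which group they are in.
4. State that those who make the weekly calls do not conduct the 30-day 30CST or CPET.

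Asking the assessor to record a guess of the arm after testing is optional.

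The cost is reformatting one form, amending a few sentences and separating roles among collaborators whom the protocol already describes. No visits are added, and the sample size and planned tests do not change.

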### 3.0 Physical fitness after Cardiac Rehabilitation

The state of sedentary lifestyle is already pointed out in the scientific literature as a risk factor crucial for primary and secondary cardiac events (23). In correlation with this finding, other studies demonstrate the level of cardiorespiratory fitness (CRF), a component of physical fitness, as the greatest predictor of mortality compared to any other cardiovascular risk factor. Therefore, ACR has been evaluated in several studies that seek to verify the benefits of CR, due to its

notorious modification during treatment. Previous work has shown an average gain of 11 to 36% in ACR after traditional outpatient CR, with greater gains in patients who had lower ACR levels at the beginning of the program (24). Thus, there is sufficient evidence to prove that improvements in ACR can explain most of the physical, psychological, and functional benefits, as well as the clinical outcomes of mortality and hospitalization after carrying out a formal CR program (10,25–27).

Among the physiological effects promoted by the physical component of CR that may justify the ACR gains and their repercussions for the general health status after the program are: Attenuation of the severity of ischemia induced by exertion with improvement of angina at rest by raising ischemic thresholds and improvement of endothelial dysfunction, increase in peak oxygen consumption and maximal aerobic power with improvement in skeletal muscle oxidative capacity, reduction in neurohumoral exacerbation, favorable action on the lipid profile, especially in cases of hypertriglyceridemia, decreased levels of HDL-cholesterol and changes in LDL-cholesterol subfractions, hypotensive effect of exercise with reduction of systolic and diastolic pressure levels (9).

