All patients will be monitored before, during, and after each supervised care session with a frequency meter and pulse oximeter (Model Nonin Onyx 9500, Nonin Medical, USA and Polar H10), which will allow the assessment of heart rate and O2 saturation. Blood pressure will be evaluated before and after the session and during the ICU stay the electrocardiogram will be monitored throughout the exercise. Patients will be instructed to interrupt the exercise in case of malaise (dyspnea, excessive sweating, cyanosis, use of accessory muscles, vertigo, retching), chest pain, or borg greater than 13 for both dyspnea and muscle fatigue.

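### A fall in systolic pressure is to be reported as an adverse event during and after sessions, but pressure is read only before and after, so a transient symptom-free fall during exercise is not captured

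*Protocol*

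**What the plan says.** Three places in the protocol bear on this point.

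- **Cardiohemodinamic safety of early cardiac rehabilitation.** Safety is assessed through adverse events notified during and after the sessions of the intervention group, session by session. The main events include "drop in systolic blood pressure (SBP) above 10 mmHg".
- **Early cardiac rehabilitation program, monitoring paragraph.** Heart rate and oxygen saturation are followed throughout: "All patients will be monitored before, during, and after each supervised care session with a frequency meter and pulse oximeter". In the ICU the ECG is also followed during exercise. Pressure is treated separately: "Blood pressure will be evaluated before and after the session".
- **Appendix A, Physical examination per session.** Each block has one line beginning "Session start: HR" and one beginning "End of session: HR". Each line ends in a blood pressure field. A tick box then reads "Fall of SBP>=10mmHg". There is no field for a reading in between.

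The protocol does not set a pressure reading during a session, the timing of the end reading, a repeat reading, or a symptom condition for the event. In the cardiopulmonary exercise test, by contrast, it schedules pressure every two minutes.

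**The concern.** The event and the measurement do not cover the same window. The safety section counts falls that occur while the patient exercises, but no pressure is scheduled then. The only fall the recorded data can yield is the difference between the start and end readings.

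Two consequences follow. A fall under load that causes no symptoms and has recovered by the end reading leaves no trace beyond what chance would flag. In addition, one pair of readings with no repeat will sometimes differ by more than 10 mmHg through measurement variation alone, and the form counts that as an event.

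Safety is part of the primary objective, and the adverse event rate is a named secondary objective. An analysis plan can choose how to tabulate readings, but it cannot recover one that was never taken. Events are notified for the intervention group only, so no control rate would show how many flagged falls are background.

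**Working it through.** The protocol gives no expected rate for this event, so there is no figure to reproduce. The check has two parts.

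**1. What the scheduled readings can show**

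| Course of systolic pressure | Start and end readings | Recorded as an SBP fall? |
|---|---|---|
| Falls during exercise, still low at the end | End below start | Yes, if over the threshold |
| Falls during exercise with symptoms, recovers | No systematic difference | Not systematically; may appear through the symptoms that stop exercise or the form's free-text field |
| Falls during exercise without symptoms, recovers | No systematic difference | No more often than by chance |
| Lower only after exercise | End below start | Yes, if over the threshold |
| No true change | Differ by noise only | Sometimes (part 2) |

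The third row is the gap.

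**2. How often noise alone is flagged**

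Inputs from the protocol:
- intervention patients: 12 (Sampling and Recruitment);
- sessions per patient: 8 to 10 on average (Early cardiac rehabilitation program);
- threshold: a fall above 10 mmHg (Cardiohemodinamic safety section).

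Sessions in total: 12 × 8 = 96 to 12 × 10 = 120. The form has pressure fields for eight sessions and only an open adverse-event question for surplus ones. The upper figure therefore presumes that falls in later sessions are assessed in the same way.

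Assumptions not in the documents: the end-minus-start difference is normal with mean 0 and SD 5, 8 or 10 mmHg.

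P(flag per session) = Φ(−10/SD). Expected flags = P × number of sessions.

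| SD (mmHg) | −10/SD | P per session | Expected in 96 | Expected in 120 |
|---|---|---|---|---|
| 5 | −2.00 | 2.3% | 2.2 | 2.7 |
| 8 | −1.25 | 10.6% | 10.1 | 12.7 |
| 10 | −1.00 | 15.9% | 15.2 | 19.0 |

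The expected counts do not need sessions to be independent. The share of patients with at least one flag would, and independence within a patient is doubtful, so I stop at counts.

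A fall that has fully recovered by the end reading is flagged at these same rates, that is, no more often than no fall at all.

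**The case against.** The best case for leaving the plan alone has four parts.

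- **Much is still caught.** Persistent falls are recorded, and symptomatic ones can surface through the stop symptoms or the free-text field. This stands. A reader might infer that falls during exercise are never detected; the documents do not support that. The loss is confined to the transient, symptom-free fall. How often that occurs in low-risk patients exercising at 2 to 3 METs is not stated.
- **The noise figures are assumptions.** This also stands. At the low end they amount to 2 or 3 events. A reader might infer that this item will dominate the adverse event count, but the protocol gives no rates for the other events, so that cannot be said.
- **Raw readings are kept.** End-of-session falls can be tabulated separately without changing the protocol. That is true, but it does nothing for the missing reading during exercise.
- **External safety criteria are cited.** These might include pressure checks. Their content is not in the protocol, and its own schedule and form have none.

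A further tempting reading is that the plan counts its own expected benefit as harm, because the introduction mentions a "hypotensive effect of exercise with reduction of systolic and diastolic pressure levels". That phrase stands in a list of physiological effects offered to explain fitness gains and health after a programme, beside lipid and endothelial changes. It does not describe a drop after one session. The Risks and Benefits section lists hypotension among the risks of physical activity. The documents therefore do not support assuming an average fall after each session, nor taking end-of-session falls out of the adverse event rate. The latter would also conflict with the safety section, which covers events after sessions.

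**Conclusion.** The mismatch holds on the text. The event window includes the exercise itself, while pressure is scheduled and recorded only at its two ends. The plan therefore does not capture a transient symptom-free fall during exercise, and it counts some reading noise as events.

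With an assumed SD of 5 to 10 mmHg and no true change, noise accounts for about 2% to 16% of sessions, or roughly 2 to 19 events in 96 to 120 sessions. The width of that range reflects how little the protocol says. The SD is not in the documents, and only the 12 intervention patients contribute. The number of falls missed cannot be estimated from the documents.

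This limits what can be claimed about safety. It does not touch the efficacy comparison, and the Statistic Strategy attaches no test to this event. It still merits a change, because safety is in the primary objective and the gap can be closed cheaply.

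The text (above 10 mmHg) and the form (10 mmHg or more) also disagree on the threshold. That is a separate inconsistency to reconcile. It does not cause the gap described here.

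**What to change.** Reconcile the monitoring paragraph, the safety section and the Appendix A form:

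1. Add one blood pressure reading during the aerobic block of each supervised session. For walking and stair blocks, where a cuff reading means stopping, take it at the immediate end of the block.
2. Add a matching field to each session block of the form.
3. Report during-session and end-of-session systolic falls on separate lines, each split by presence or absence of symptoms, and keep both in the safety report.

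If no such reading is added, restrict the safety statement on systolic falls to end-of-session change and say so in the safety section.

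This concerns what is measured and how it is reported; no threshold or stopping rule is proposed. The extra reading does not remove noise, since it too is a single value compared with the start. Separate lines keep the two kinds of fall distinguishable. The cost is a brief interruption and one more value to record per session, with staff and equipment already present.
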